#### Construct Validity

The construct validity of the SPARS adherence measures will be evaluated using cross-validated exercise type and technique classification performance metrics (accuracy, precision, recall, and f1-score) from the labeled inertial data. The cross-validated metrics will be assessed for 3 different fold splitting strategies: (1) by-subject; (2) by-session; and (3) within-session. Respectively, these estimate SPARS performance for (1) new subjects (with no training data); (2) new sessions for subjects with prior training data; and (3) new exercise repetitions within a session from which training data were acquired. The by-session cross-validation most closely approximates the use case in the proposed study and will benchmark SPARS performance against our stated measurable objectives.

#### Concurrent Validity

Concurrent validity of SPARS will be established with (1) patient home exercise adherence diaries; and (2) physiotherapist exercise logs recorded in the absence of the researchers. The number and type of exercises measured by SPARS will be evaluated against both the adherence diaries and physiotherapist logs. The evaluations of the SPARS technique will be compared with the physiotherapist logs. Systematic bias between measurement methods will be evaluated using a paired sample *t* test and Bland-Altman plots [125]. Reproducibility will be evaluated using an intraclass correlation with a 2-way random-effects model for absolute agreement interclass correlation coefficient (2,1) [126].

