#### Inertial Data Labeling

The researchers will attend a supervised physiotherapy session for each patient once every 2 weeks to record exercise type and technique labels synchronously with inertial data collection, based on the input from the treating physiotherapist. The technique will be labeled as a binary variable, indicating if the treating physiotherapist was satisfied that the exercise was performed correctly (as intended). The treating physiotherapist will also make a record of prescribed home exercises and exercise type and technique evaluations at each supervised physiotherapy session.

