#### Home Physiotherapy Adherence Diaries

Patients will log their home physiotherapy activities in an adherence diary for 2 weeks, during the strengthening phase of their rehabilitation. Validation of the SPARS adherence measurement will include a comparison with these data.

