#### Smart Physiotherapy Activity Recognition System-Home Physiotherapy Participation Adherence

The ML algorithms underlying SPARS will be trained in a supervised learning framework to classify (recognize) different activities from the characteristic time series of inertial signals they produce in the smart watch inertial sensors. A detailed description of our implementation and its evaluation are presented in our previous pilot study [15] and our open-source software package for ML time series (seglearn) [116]. Briefly, sensor data are segmented into fixed-length windows (2-4 sec in length) that are learned by a deep convolutional recurrent neural network (CRNN) classifier. Once trained, the classifier can be used to reconstruct a record of activities from the recorded inertial sensor data.

The ML algorithms underlying SPARS will be trained and validated using the labeled inertial sensor data collected during supervised physiotherapy sessions. The trained SPARS algorithms will then generate a record of exercises performed from inertial sensor data collected during unsupervised home sessions and supervised sessions during which synchronous data labeling was not performed. Comparing the quantity and frequency of home exercises measured by SPARS with the prescribed exercises will serve as our measure of participation adherence. Participation adherence will be measured as a percentage of the prescribed activity over each 2-week interval of treatment.

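### The home diary comparison tests agreement on exercise counts, not on percentage of prescription, so its ICC can overstate agreement on adherence if prescribed volumes differ between patients

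*Protocol article*

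**What the plan says.** The section on home participation adherence defines the measure: "Participation adherence will be measured as a percentage of the prescribed activity over each 2-week interval of treatment". The section on adherence diaries sets the comparator and its window, "Patients will log their home physiotherapy activities in an adherence diary for 2 weeks, during the strengthening phase of their rehabilitation", and its purpose: "Validation of the SPARS adherence measurement will include a comparison with these data". The Discussion gives the same purpose, setting measured adherence against patient self-report.

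Concurrent Validity names the quantity compared: "The number and type of exercises measured by SPARS will be evaluated against both the adherence diaries and physiotherapist logs". It then names the statistics: "Systematic bias between measurement methods will be evaluated using a paired sample" *t* test and Bland-Altman plots, and for reproducibility, "Reproducibility will be evaluated using an intraclass correlation with a 2-way random-effects model for absolute agreement", that is, ICC(2,1). It does not say that the counts are divided by the prescription, and it sets no ICC target.

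The denominator is collected. Inertial Data Labeling states: "The treating physiotherapist will also make a record of prescribed home exercises and exercise type and technique evaluations at each supervised physiotherapy session".

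**The concern.** The diary comparison is meant to validate an adherence measure, but the quantity named for it is a count. The two scales differ by the prescribed volume, which is the same for SPARS and for the diary in any one patient.

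An ICC is between-patient variance divided by total variance. A patient prescribed many exercises tends to have a high count by both methods, and a patient prescribed few a low count by both. That variance counts as agreement, although it says nothing about how well either method measures the share of the prescription that was done.

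The later uses need that share. Criterion Validity relates adherence to outcome, the univariable and multivariable analyses model adherence from baseline predictors, and the pilot lets clinicians act on it. A count ICC does not describe the measurement error that enters those uses.

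**Working it through.** **No figure to reproduce.** The article gives no ICC value, target or precision, and no spread of prescribed volume. All numerical inputs below are assumptions.

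**Model.** For each patient, prescribed volume P has coefficient of variation c. True adherence has mean m and SD s. SPARS and the diary have independent errors in percentage points, with mean error variance v. P is independent of adherence and of the errors, there is no systematic bias, and each patient contributes one pair. Each count is P times measured adherence, with the same P for both methods.

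**Formulas.**
- Percentage scale: ICC = s² / (s² + v).
- Count scale (P scaled to mean 1): shared variance B = s²(1 + c²) + m²c²; error variance W = v(1 + c²); ICC = B / (B + W).

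The term m²c² is the part contributed by the prescription alone.

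**Main inputs.** m = 0.60, s = 0.25, error SDs 0.25 and 0.175, so v = (0.0625 + 0.030625)/2 = 0.04656.

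Percentage scale: 0.0625 / (0.0625 + 0.04656) = 0.57.

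| CV of prescribed volume | B | W | ICC on counts |
|---|---|---|---|
| 10% | 0.0631 + 0.0036 = 0.0667 | 0.0470 | 0.59 |
| 20% | 0.0650 + 0.0144 = 0.0794 | 0.0484 | 0.62 |
| 40% | 0.0725 + 0.0576 = 0.1301 | 0.0540 | 0.71 |
| 60% | 0.0850 + 0.1296 = 0.2146 | 0.0633 | 0.77 |

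**Sensitivity to the inputs.**
- Smaller errors (15 and 10.5 points, s = 0.25): v = (0.0225 + 0.011025)/2 = 0.01676. The ICC is 0.79 on percentages and 0.82, 0.87 and 0.90 on counts at CV 20%, 40% and 60%.
- s = 0.20, error SD 0.20 for both methods: 0.50 on percentages; 0.60, 0.74 and 0.81 on counts at CV 25%, 50% and 75%.
- Adherence varying little between patients (s = 0.10, error SD 0.10): 0.50 on percentages; 0.58, 0.76, 0.89 and 0.93 on counts at CV 10%, 25%, 50% and 75%. The gain of 0.08 at CV 10% is the largest at that CV among the settings tried.
- No agreement at all on adherence, measured SD 0.20: ICC on counts = m²c² / (m²c² + 0.04(1 + c²)). At CV 25% this is 0.0225/(0.0225 + 0.0425) = 0.35; at CV 50% it is 0.64.

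**Sampling at N = 120** (2,000 simulated cohorts, s = 0.15, error SD 0.15, CV 50%): median ICC 0.50 (95% range 0.35 to 0.62) on percentages and 0.81 (0.69 to 0.88) on counts. With those inputs the gap is larger than sampling noise.

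**Bland-Altman and *t* test.** Both use within-pair differences, so a shared prescription does not flatter them as it does the ICC. The units remain a problem: a difference of 5 exercises is 25 adherence points if 20 were prescribed and 5 points if 100 were.

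**The case against.** The strongest reply is that counts are what SPARS produces directly, and the prescription is an outside record common to both methods. Comparing an instrument's output with another record of the same output is a legitimate form of concurrent validity. The paired *t* test and Bland-Altman plots accompany the ICC. The numerical benchmarks are classification accuracies above 90% and 80%, judged by by-session cross-validation, and no decision hangs on an ICC threshold. Nor do the statements of purpose exclude a percentage analysis. All of this stands, and it makes the point a correction of scale rather than a flaw in the design. It does not remove the mismatch: the article fixes the variable and the statistic, and the variable is not the one it defines as adherence.

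A reader might infer three stronger things that the documents do not support.

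- *That the ICC is inflated.* This needs a spread of prescribed volume that the article does not give. Conservative and operative patients are both eligible, which makes differences plausible, but the diary covers only 2 weeks of one phase, which may narrow them.
- *That poorly measured adherence could show an excellent ICC.* If excellent means above 0.90, the calculations reach it only with a CV of about 75% or more and little variation in adherence between patients. Moderate-to-good values are more typical.
- *That the physiotherapist-log comparison has the same fault.* Those logs concern supervised sessions. The adherence percentage is defined for home exercise, and the article defines no prescribed amount for a clinic session. For the logs the question is whether SPARS counts correctly, and counts are the natural scale.

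**Conclusion.** The point holds for the home diary comparison. The named quantity is the number of exercises, while the measure being validated is a percentage of prescription. If prescriptions differ, the count ICC exceeds the adherence ICC. Under the main assumptions it rises from 0.57 to between 0.62 and 0.77 for a CV of 20% to 60%, and by about 0.01 at CV 10%. The direction follows from the formula when prescribed volume is independent of adherence and error. The size depends on the unreported spread of prescriptions and on the assumed adherence and error SDs. Count-based limits of agreement are not flattered in the same way, but they cannot be read as adherence points.

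**What to change.** In Concurrent Validity, state that for the diary comparison the bias, limits of agreement and ICC(2,1) are computed on the adherence scale: SPARS number divided by prescribed number against diary number divided by prescribed number, over the same 2 weeks and in percentage points. Report the count comparison as supporting. Giving the mean and SD of prescribed volume over that interval would show how far the two scales can diverge.

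Keep counts for the physiotherapist-log comparison, and add that its ICC is not evidence on how well home adherence is measured.

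The cost is a sentence or two and one division per patient. The denominator is already recorded, and the adherence measure needs it anyway. The only downside is that the reported ICC may be lower.

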#### Criterion Validity

Changes in clinical outcomes will be evaluated as a function of SPARS adherence measures using univariate linear regression analysis, with management subgroup (conservative or operative) and population subgroup (worker or patient) as moderators. This analysis will examine both the concurrent and predictive effects of home physiotherapy adherence on clinical outcomes.

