**Objective:**

The proposed research will (1) validate a smartwatch and machine learning (ML) approach for evaluating adherence to shoulder exercise participation and technique in a clinical patient population with rotator cuff pathology; (2) quantify the rate of home physiotherapy adherence, determine the effects of adherence on recovery, and identify barriers to successful adherence; and (3) develop and pilot test an ethically conscious adherence-driven rehabilitation program that individualizes patient care based on their capacity to effectively participate in their home physiotherapy.

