### Adherence to Rehabilitation

Adherence is defined as the extent to which the patient follows medical instructions [43]. There is a general assumption that, where a treatment program is efficacious, adherence to the program improves outcome. Patient adherence to a prescribed physiotherapy has been shown to be an important predictor for the successful management of musculoskeletal disorders [9]. However, adherence to standard exercise protocols is often poor with estimates of non or partial nonadherence varying between 50% and 70% [9,11], with worse adherence for home exercise protocols [9].

In the context of physiotherapy and rehabilitation, the concept of adherence is multidimensional [44]. It includes behaviors such as attending clinical appointments, actively participating in physiotherapist-supervised rehabilitation activities, carrying out home exercise and rehabilitation activities, avoiding potentially harmful and contraindicated activities, and wearing protective or therapeutic devices [44]. Physiotherapy clinic attendance is readily measured, and the Sport Injury Rehabilitation Adherence Scale [44] has been used for evaluating in-clinic adherence. The correct use of protective devices has been measured by observations at clinical follow-up [10] and with temperature sensors [45-47].

Measuring adherence to home physiotherapy exercises remains an open problem [48]. Adherence to this component of a rehabilitation program is particularly vital as this activity calls for the greatest level of independent patient engagement in the rehabilitation process. Adherence diaries, in which patients log their independent exercises, is the recommended and most widely used measure of adherence to home exercise [48]. However, adherence diaries have significant limitations. The validity and reliability of the adherence diary have not been established, and poor patient acceptability results in low rates of diary completion [48]. Furthermore, the written diary has no means to establish if the prescribed exercises have been performed correctly. The proposed study will validate a novel method for measuring participation and technique adherence to home shoulder physiotherapy exercises.

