### Adherence to Rotator Cuff Rehabilitation

Several studies on patients with rotator cuff pathology have measured rehabilitation adherence variables, including clinic attendance, adherence to postoperative restrictions, and home physiotherapy participation during rotator cuff rehabilitation [4,10,13,26,49-51]. Nonadherence (eg, to protective device use and clinic attendance) is more prevalent in workers’ compensation patients (52%) than nonworkers (4%) [10]. There is also a relationship between adherence and improved clinical outcomes in the nonoperative [50] and operative management [10,51] of rotator cuff pathology.

Unfortunately, adherence to home rotator cuff exercises has only been measured with adherence diaries [4,26,50] or in response to directed questioning [51]. The completion rates for the adherence diaries varied from 60% to 75% [4,26,50]. Furthermore, the validity of a patient’s self-reported adherence is questionable as a research instrument [52]. Therefore, the rate and effect of adherence to home rotator cuff exercise participation and technique remain unknown. The proposed study will address this knowledge gap in a cohort of 120 patients with rotator cuff pathology.

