#### Inertial Data Collection

Each study subject will be provided with a smart watch to be worn on their affected extremity when performing the prescribed physiotherapy exercise. The smart watch must be worn for all physiotherapy exercise sessions conducted over the duration of treatment, up to a maximum of 5 months. This includes all supervised physiotherapy sessions at the Holland Centre and any physiotherapy exercise sessions conducted by the patient independently (home exercises). No alteration to the prescribed physiotherapy will be undertaken during this clinical validation study.

The smart watches purchased for this study will have a 9-axis IMU (3-axis accelerometer, 3-axis gyroscope, and 3-axis magnetometer). The inertial sensors will be sampled at 50 Hz and recorded to the internal memory storage on the smart watch. The inertial data will be encrypted using the Rivest–Shamir–Adleman public-key cryptosystem. The smart watch will permit up to 150 hours of sensor data recording to its 4 GB internal memory. The sensor data will be retrieved and removed from the smart watch when the patient attends supervised physiotherapy at the Holland Centre (2 times per week).

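### The home-adherence effect on recovery is estimated without the supervised exercise the same patients receive, so part of any attendance effect can be credited to home exercise

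*Protocol article*

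**What the plan says.** The Abstract's Objective sets out to "determine the effects of adherence on recovery". Criterion Validity names the model for this: change in clinical outcome is regressed on the SPARS adherence measures "using univariate linear regression analysis, with management subgroup (conservative or operative) and population subgroup (worker or patient) as moderators". It then states how the result will be read: "This analysis will examine both the concurrent and predictive effects of home physiotherapy adherence on clinical outcomes".

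The participation exposure is home exercise only: "Comparing the quantity and frequency of home exercises measured by SPARS with the prescribed exercises will serve as our measure of participation adherence".

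The same patients also exercise under supervision. Inertial Data Collection says that home data come off the watch "when the patient attends supervised physiotherapy at the Holland Centre (2 times per week"), during a treatment period of at most 5 months. The requirement to wear the watch covers the clinic: "This includes all supervised physiotherapy sessions at the Holland Centre". The section on participation adherence adds that SPARS will also produce an exercise record for supervised sessions that were not labeled live. The Introduction (Adherence to Rehabilitation) notes: "Physiotherapy clinic attendance is readily measured".

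Two other places could have brought supervised exercise into the recovery model, and neither does. The Abstract's Methods mentions multivariate outcome analyses, but names adherence and baseline variables. Univariable and Multivariable Analyses has a home-or-clinic term, but in a model where adherence is the dependent variable.

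**The concern.** Patients receive two exercise components at once, and the recovery model contains only one of them. If patients who are diligent at home are also those who attend, the home coefficient absorbs whatever attendance contributes. The two moderators do not prevent this, because neither measures how much supervised exercise a patient received. Baseline covariates do not measure it either, since supervised exercise accrues during treatment.

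Two conclusions depend on the home coefficient. Aim 2 concerns home physiotherapy specifically, and the pilot program acts on measured home adherence. The Discussion would also take a positive adherence-recovery relationship as further evidence that the algorithm is valid. That inference is weaker if the relationship could arise through attendance.

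**Working it through.** **Inputs from the protocol.** N = 120, 80% power, R = 0.25, alpha 5% (Sample Size; sidedness not stated, two-sided taken). Two supervised sessions a week for up to 5 months: 5 × 52/12 ≈ 21.7 weeks, × 2 ≈ 43 sessions for a full attender over the full period.

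**Inputs not in the protocol.** The correlation of home adherence with attendance (a) and of attendance with outcome (b). Both are assumed and varied below.

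**Step 1: the plan's own figure.** Fisher z, two-sided: power = Φ(atanh(r)·√(n−3) − 1.96), plus the negligible opposite tail. With r = 0.25 and n = 120: 0.2554 × 10.817 = 2.763, and 2.763 − 1.960 = 0.803, so power is 78.9%. The noncentral t gives 80.1%. The stated 80% is reproduced, and the sample size is not in question.

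**Step 2: bias with no true home effect.** If home adherence does nothing and is linked to outcome only through attendance, the expected home-outcome correlation is a × b. Putting this into the Step 1 formula, with both tails, at n = 120:

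| a | b | a × b | P<.05 in |
|---|---|---|---|
| 0.1 | 0.1 | 0.01 | 5.1% |
| 0.3 | 0.3 | 0.09 | 16.4% |
| 0.5 | 0.3 | 0.15 | 37.3% |
| 0.6 | 0.4 | 0.24 | 75% |
| 0.5 | 0.5 | 0.25 | 78.9% |

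For the fourth row: atanh(0.24) × 10.817 = 2.648, and 2.648 − 1.960 = 0.688, giving 75%. In the last row the bias alone equals the R the study is sized to detect. In the first row there is no material bias.

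**Step 3: what adjustment does.** In 4,000 simulated studies of 120 patients per setting, with no home effect, the univariate test rejected in 16.3%, 36.6% and 78.5% for (a, b) = (0.3, 0.3), (0.5, 0.3) and (0.5, 0.5). With attendance as a covariate it rejected in 5.1%, 4.8% and 5.2%. The simulation treats attendance as a pure confounder, so the return to 5% is built in. It shows the mechanism and does not show that real attendance behaves this way.

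**Step 4: price of adjustment.** One covariate changes √(n−3) to √(n−4). For a partial r of 0.25: 0.2554 × 10.770 = 2.751, and 2.751 − 1.960 = 0.791, so power is 78.6% against 78.9%. For a fixed slope, the standard error also grows by 1/√(1−a²), before any gain from smaller residual variance: 1.15 at a = 0.5 and 1.25 at a = 0.6.

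**The case against.** The strongest reply has five parts.

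- **Link to outcome.** A reader might infer that the protocol itself establishes an attendance-outcome link from "There is also a relationship between adherence and improved clinical outcomes in the nonoperative". It does not do so cleanly. That sentence cites references 50, 10 and 51. The next paragraph identifies 50 and 51 as measuring home adherence, by diary and by questioning. Only reference 10 concerns attendance, mixed with protective-device use and cited for operative patients. This stands.
- **Link to home adherence.** A reader might take low in-treatment adherence, listed under Factors Affecting Adherence, as showing that attendance and home adherence go together. That list comes from a review of supervised clinics in which most studies counted appointments, and the section concludes that barriers to home exercise remain uncertain. This stands: the protocol neither supports nor excludes the link.
- **A multivariate analysis is planned.** The Abstract says so, and an article may leave the full covariate list elsewhere. But what it names is adherence and baseline variables, and Criterion Validity spells out its model and its moderators. The reply does not meet the point.
- **Only association is claimed.** The Aim 2 hypothesis says association, and Sample Size refers to correlations. An unadjusted estimate answers that question properly. The Objective and Criterion Validity nevertheless speak of effects, the latter specifically of home adherence, so the gap between model and conclusion remains.
- **Adjustment can itself mislead.** Treatment length is variable. Patients who recover early may stop and slow recoverers may continue, so a raw session count could partly reflect the outcome. Attendance could also respond to earlier home exercise. This stands, and it rules out making the adjusted coefficient the sole basis of the conclusion.

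**Conclusion.** The point holds in a conditional form. As written, the model cannot separate a home-specific effect from supervised exercise that the same patients receive and the same watch records. Part of an attendance effect can therefore be credited to home exercise.

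It would go too far to say that it is credited. That requires attendance to vary, to go with home adherence and to affect outcome, and the protocol quantifies none of these. The false-positive rate for a null home effect runs from about 5% (0.1 and 0.1) through 37% (0.5 and 0.3) to 75% (0.6 and 0.4), entirely according to assumed correlations.

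This is a cheap improvement that changes what may be concluded about home exercise. It does not invalidate the association analysis or the sample size.

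**What to change.** In Criterion Validity, keep the unadjusted estimate and report next to it one adjusted for supervised attendance over the same exposure window. Express attendance as the proportion of scheduled sessions attended. A raw count depends on treatment length and possibly on recovery.

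Claim a home-specific effect only if the two estimates agree, and state beforehand what counts as agreement. Otherwise describe the result as an association with overall rehabilitation adherence.

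**Cost.** One covariate, with the numerator obtainable from sessions already recorded and the denominator from the clinic schedule. The loss of power for a given partial correlation is negligible (78.9% to 78.6%), but the interval widens if attendance and home adherence are strongly correlated. Attendance is post-baseline and may itself be affected by recovery, so the adjusted estimate supplements the unadjusted one and does not replace it. It also leaves other confounders untouched.
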